### Hypotheses

The RCT will address 2 primary hypotheses. Hypothesis 1 has 7 secondary hypotheses. Compared with the control group,

Significantly more intervention group patients will receive specialty SUD care within 30 days following the SBIRT encounter at the primary care clinic. The secondary hypotheses attempt to explain how and where the increased specialty care utilization occurs in the process.More intervention group patients are diagnosed with high-risk SUD.More intervention group patients are subsequently referred to specialty care at the end of the primary care clinic encounter.More intervention group patients are referred to specialty care during the 30-day following period due to failing to adhere to goals.Intervention group patients are more satisfied with the care they receive.Intervention group patients are more knowledgeable about SUD.Intervention group clinicians are more satisfied with the process.Intervention group clinicians spend less time on the SBIRT intervention and follow-up.Intervention group patients will report a greater reduction in substance use and a greater drop in Drug Abuse Screening Test (DAST-10) and Addiction Severity Index (ASI) scores within 30 days.

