#### Surveys

At the end of the primary care clinic visit, all participants will be asked to complete a survey about their experience with the process and their knowledge about SUDs. The intervention group patients will also be asked about their acceptance of the technology solution. The survey has the following components:

A 19-item validated computer system usability questionnaire is used to evaluate a computer system’s usability [33]. It also allows users to give free form answers on what he or she likes or dislikes about the system. We use it to evaluate the iPad tool in primary care clinics.A questionnaire based on the unified theory of acceptance and use of technology (UTAUT) by Venkatesh et al [34] is used to evaluate the technology solution’s ease-of-use, perceived usefulness, and the user’s social and facilitating conditions to predict the adoption of such technology solutions. The original UTAUT questions will be adapted to reflect our product.A 10-item validated patient satisfaction questionnaire will evaluate patient satisfaction with primary care providers [35].The ASI–Lite asks for drug use in the previous month, comorbid medical and mental illness, and social and legal outcomes related to drug use [36]. The ASI score is a quantitative measure of the user’s substance use.

At the end of the 30-day follow-up period, all participants will be asked to complete the screening, patient satisfaction, and ASI questionnaires again. They will also be asked to report any health care service they received during the 30 days, including any specialty SUD services. They can complete those questions on a computer or on paper. A complete schedule of all participant surveys and questionnaires is listed in Table 1.

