#### Hypotheses Testing

Since the hypotheses are primarily concerned about the observed differences between control and intervention arms, including referral rates, satisfaction level, knowledge level, and greater reduction in substance use, Student *t* tests will be used.

A chi-square test will be performed on the proportions of participants who receive specialty care to detect the significance in the difference between control and intervention arms. This test will be repeated for participants who have self-reported receiving specialty care. A chi-square test will be performed on the proportions of participants who receive specialty care referral at the end of the primary care encounter and who receive a specialty care referral during the 30-day follow-up period. For each question in the participant satisfaction survey and on the overall computed satisfaction and knowledge score, we will perform a *t* test for the answer’s mean value. Clinician interview results will be evaluated qualitatively to determine clinicians’ satisfaction with the solution.

Difference in differences regression tests will be performed on the differences in self-reported substance use amount and frequency and DAST-10 scores measured at baseline and 30 days of the study. The correlation coefficients and their confidence levels will be computed. These tests detect difference in drug use changes from control and intervention groups during the intervention period.

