#### Power Calculation

For primary hypothesis 1, we will perform a chi-square test to evaluate the difference in proportions of participants who receive specialty care in the 2 arms. We estimate that SBIRT intervention [37] could result in 10% to 30% of patients receiving specialty care. We computed power using the following assumptions: chi-square for 2 proportions, 2 samples, and 2-sided test; type 1 error rate of 5%; power of 0.9; control arm with 20% participants receiving specialty care; intervention arm with 35% participants receiving specialty care; and same number of participants in control and intervention. A sample of 197 participants in each of arms will be sufficiently powered to detect such differences between control and intervention arms.

For primary hypothesis 2, we assume that both arms start with the same levels of substance use. Therefore, to test the hypothesis, we will test the mean substance use levels at 30 days for both arms. We computed power for the sample *t* test of the mean using the following assumptions: 2-tailed *t* test for the mean of 2 samples; type 1 error rate of 5%; power of 0.9; medium Cohen effect size; and same number of participants in control and intervention. A sample of 86 participants in each arm will produce sufficient power. Based on the above calculation and considering up to 20% attrition, a sample of 500 total participants will have sufficient power to test both primary hypotheses.

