## Results

In phase 1 of this project, we developed and piloted a prototype solution to enhance SBIRT in primary care office and follow up patients intensively for 30 days. The prototype proved feasibility of the technology, including the innovative user interface, dynamic screening logic, computerized brief intervention, shared-screen SDM, and bidirectional EMR connectivity. Our pilot clinicians and patients overwhelmingly determined the tool to be easy to use and not intrusive to normal clinical workflows. Patients with low-risk SUDs were also able to adhere to the shared goals during the follow-up period.

In phase 2 of this project, we supposed that, compared with the control group participants at 30 days, (1) significantly more intervention group patients will receive specialty SUD care and (2) intervention group patients will report a greater reduction in substance use and a greater drop in DAST-10 scores. Our secondary hypotheses include that intervention group patients receive more referrals at the primary care clinic and during 30 days of follow-up, and both clinicians and patients are more satisfied with the technology-enhanced solution.

Data collection for phase 2 is well underway. We expect to report the data analysis results in early 2018.

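### The single satisfaction hypothesis is tested by 11 t tests of equal standing at each visit, which lifts the chance of a false result favouring the intervention from 2.5% to about 9% to 18%

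*Protocol article*

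**What the plan says.** - **Hypothesis.** The Hypotheses section of the protocol article lists, as one of seven secondary hypotheses under primary hypothesis 1, "Intervention group patients are more satisfied with the care they receive". It names no item, score or visit. The Results section restates it within a list of secondary hypotheses: "both clinicians and patients are more satisfied with the technology-enhanced solution".
- **Instrument.** The Surveys section says "A 10-item validated patient satisfaction questionnaire will evaluate patient satisfaction with primary care providers".
- **Timing.** The Surveys section schedules it twice in both arms: "At the end of the primary care clinic visit, all participants will be asked to complete a survey about their experience with the process", and then "At the end of the 30-day follow-up period, all participants will be asked to complete the screening, patient satisfaction, and ASI questionnaires again". Table 1 marks patient satisfaction at both points for both arms.
- **Analysis.** The Hypotheses Testing section plans a t test of the mean "For each question in the participant satisfaction survey and on the overall computed satisfaction and knowledge score". It does not say whether these tests are run at one visit or both. The item tests are not placed in the separate Exploratory Analysis section.
- **Error rate.** The Power Calculation section gives a two-sided "type 1 error rate of 5" percent, but only for the two primary hypotheses.

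**The concern.** One claim is attached to 11 tests at a visit, and the article gives the item tests the same standing as the overall score. A significant difference on any single item could therefore be read as support for greater satisfaction. Each test may hold its own 5% level, but the claim as a whole does not.

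The two administrations add a further choice. The first comes at the end of the clinic visit, before any mobile follow-up. The second comes after 30 days of it in the intervention arm. They reflect different exposures and could disagree.

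What is at stake is limited but real. The secondary hypotheses are meant to explain how and where any increase in specialty care arises, and satisfaction is one proposed step. A chance item-level difference could be mistaken for part of that explanation.

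**Working it through.** **The plan's own figures.** The article states no error rate or sample size for satisfaction, so there is nothing to reproduce for this family. Its stated sizes for the primaries do reproduce. For 20% against 35%, two-sided 5% and power 0.9, the continuity-corrected formula gives 198 per arm against the stated 197. A two-sample t test with a standardised effect of 0.5 needs 85.03, hence the stated 86. Neither bears on this point.

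**Inputs**
- From the article: 10 items (Surveys); one test per item plus one on the overall score (Hypotheses Testing); two administrations in both arms (Surveys, Table 1).
- Assumed: two-sided 5% per test, carried over from the primaries; equal correlation ρ between items, from 0.3 to 0.8; correlation r between visits, from 0.3 to 0.7. The article gives no correlations.

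**Step 1: number of tests.** 10 + 1 = 11 at one visit, and 2 × 11 = 22 if both visits are tested. The knowledge score belongs to another secondary hypothesis and is not counted.

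**Step 2: reference values if all tests were independent**
- 11 tests: 1 − 0.95^11 = 0.431 in any direction; 1 − 0.975^11 = 0.243 favouring the intervention.
- 22 tests: 1 − 0.95^22 = 0.676; 1 − 0.975^22 = 0.427.

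These overstate the risk, because items of one scale are correlated and the overall score is built from them.

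**Step 3: correlated tests.** For each setting, 200,000 null trials were simulated:
- 10 item z-statistics with common correlation ρ;
- the overall z as their sum divided by √(10 + 90ρ);
- second-visit statistics formed as r times the first-visit values plus √(1 − r²) times an independent set with the same item correlation.

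Trials were counted if any |z| exceeded 1.96 (any direction) or any z exceeded 1.96 (favouring the intervention).

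| ρ | 11 tests, any | 11 tests, favourable | 22 tests, any | 22 tests, favourable |
|---|---|---|---|---|
| 0.3 | 0.350–0.353 | 0.178–0.180 | 0.521–0.570 | 0.273–0.310 |
| 0.5 | 0.287–0.288 | 0.145 | 0.434–0.485 | 0.221–0.254 |
| 0.7 | 0.212–0.213 | 0.106–0.107 | 0.329–0.373 | 0.164–0.192 |
| 0.8 | 0.172–0.173 | 0.086 | 0.271–0.307 | 0.135–0.155 |

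For 22 tests the range is over r. For 11 tests r plays no part, and the small spread is simulation noise.

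**Step 4: compare with one test.** A single test gives 0.05 in any direction and 0.025 favourable. For 11 tests the favourable rate is 0.086/0.025 = 3.4 to 0.180/0.025 = 7.2 times nominal.

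**Step 5: overall score only, tested at both visits.** The any-direction rate is 0.083 to 0.095. Dropping the item tests removes most of the inflation, and naming the visit removes the rest.

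**The case against.** **A condensed article may leave this to an analysis plan.** Ranking of secondary tests, the deciding visit and descriptive labels are often settled there, and silence on them would be no finding. That is fair as far as it goes. The point survives because the article does more than stay silent: it commits to a t test on every item, under Hypotheses Testing, alongside the overall score.

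**The overall score may already be the intended test.** The opening sentence of Hypotheses Testing speaks of satisfaction level, so the items could be read as a breakdown of the score. This is plausible, but the text does not say it.

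**Stronger readings that a reader might infer**
- *That a chance finding of greater satisfaction is likely.* It is not. Such a finding must favour the intervention, and that probability stays below one half even with 22 independent tests (0.427).
- *That 22 tests are planned.* Table 1 schedules the questionnaire; Hypotheses Testing does not say that both administrations are tested. The text supports 11 tests at a visit.
- *That satisfaction is a headline claim.* It is one of seven explanatory secondary hypotheses, comes last in the list in Results, and is absent from the abstract's expected findings.

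The choice between visits is also a matter of preference. The clinic-visit score precedes the expected attrition of up to 20%; the 30-day score covers the follow-up program. Either can be defended, provided one is named in advance.

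**Conclusion.** The point holds as a moderate one about a secondary hypothesis. With 11 tests at one visit, the chance of at least one false result favouring the intervention is about 9% to 18%, against 2.5%; in any direction it is 17% to 35%, against 5%. Testing both visits would raise the favourable figure to about 14% to 31%, conditional on a reading that the article does not state.

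These figures rest on no true difference, a two-sided 5% level for each test, and the assumed correlations. The exact size moves with the item correlation, but the favourable rate is more than three times nominal at every value from 0.3 to 0.8. Neither primary hypothesis, nor the sample size, is affected.

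**What to change.** In Hypotheses Testing, state that the satisfaction hypothesis is decided by one two-sided 5% t test comparing the overall satisfaction score between arms, at one visit that the sponsor names in advance. Report the 10 item means, and the overall score at the other visit, as between-arm differences with confidence intervals, labelled descriptive, with no claim resting on them.

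This returns the error rate for the claim to 5% in any direction and 2.5% favourable. Keeping every test as confirmatory would instead need, by Bonferroni, a level of 0.05/11 = 0.0045 per test at one visit, or 0.05/22 = 0.0023 over both.

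The cost is one or two sentences. Data collection, sample size and the primary analyses stay as they are, and all item results are still reported. The small downside is that an isolated significant item, or the visit not chosen, can no longer support the claim.

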#### Exploratory Analysis

The exploratory analysis will be performed to gain further insights into additional data collected from the intervention participants. We will perform linear regression analysis to associate model technology acceptance factors with the participant’s inclination to adopt the technology in the future. This result will inform us on which factors are most important to patients for this tool. We will perform linear regression analysis to associate observed follow-up metrics such as ratio of missed questionnaires, substance use, and substance craving with participant referral decisions during the follow-up period. The result will inform a model to predict high-priority patients for referral in future interventions.

The association between mood and substance use and craving is inconclusive in existing research literature. In this project, we will collect self-reported mood and substance use/craving data from all intervention arm participants. We will group substance use/craving data into positive and negative mood categories and compare the differences using chi-square or *t* tests of the mean methods as appropriate. Furthermore, we can apply multilevel (also called mixed effect) regression models to EMA data. Mixed effects regression models can be applied to normally distributed continuous and categorical outcomes and nonnormally distributed outcomes such as counts with a Poisson distribution. Mixed effects models are also robust to missing data because time is treated as a continuous variable, the implication being that subjects are not assumed to have the same number of assessments at the same time points. To evaluate the relationship between craving, mood, and substance use, we used a generalized linear mixed model with a binary logistic response function of substance use. Fixed effects included craving for the substance and mood states.

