### Shared Decision Making, Self-Monitoring, and Ecological Momentary Assessment

As the fields of mental health care and substance abuse treatment have changed, there has been a greater emphasis on the importance of patient autonomy and patient involvement in treatment. Active patient participation is a critical component of recovery and enhances the personal meaning, treatment satisfaction, and quality of life for the patient [12]. Shared decision making (SDM) is an interactive collaborative process between the health care provider and the patient in which the practitioner becomes a consultant to the patient, providing information, discussing options, and supporting the patient’s autonomy as they mutually decide on treatment options [13]. SDM has been found to be associated with improved outcomes in substance-dependent patients, including increased personal control and reduced drug use [14-15].

One important component of SUD treatment and prevention that contributes to patient autonomy is the use of self-monitoring logs, in which patients are directed to record details about their alcohol and drug use, including their moods and the situations in which use occurred. This practice serves multiple purposes—it provides an opportunity for the patients to talk openly and honestly about their alcohol and drug use, it encourages patients to take responsibility for their own behavior change, and it provides information that providers can use to observe patterns and give feedback about changes in alcohol and drug use over time [16]. Ecological momentary assessment (EMA) is a method in which data are collected in real-world environments as subjects go about their lives. Assessments focus on subjects’ current state based on strategically selected moments (eg, occasions when subjects have craving). In EMA, subjects complete multiple assessments over time, providing a picture of how their experiences and behavior vary over time and across situations [17].

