### Trial Process

#### Timing and Flow of the Randomized Controlled Trial

We will conduct an RCT with 500 patients with SUD risk in the UHD Clinic, a large academic primary care provider affiliated with a major public university. Recruited patients will be randomized into control and intervention arms. Both arms will take initial baseline and exit (30 days) surveys to evaluate self-reported substance use and specialty service utilization. The control arm patients will receive usual care. The intervention group patients will receive technology-enhanced SBIRT with a mobile follow-up program to track goals and substance use at home. The RCT will be managed by a team of seasoned SBIRT and addiction researchers and practitioners at the research site.

The RCT tracks participants for 30 days after the primary care encounter. We will collect feedback from the patients during the 30 days and count the number of patients who use specialty care services in specialty care programs for tobacco, alcohol, and drug abuse (both from self-reporting and from the service providers).

Since the clinical trial involves more than 9 human subjects, the RCT will be approved by the OMB as well as the university’s Institutional Review Board (IRB), which is responsible for research in the university affiliated health care providers. Figure 1 displays the flow of participants.

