#### Follow-Up

The control arm participants will receive no additional follow-up beyond usual care until the 30 days’ end.

The intervention arm participants will receive a once-per-day reminder to answer daily follow-up questions. The questionnaire screen includes:

Reminder for specialty care appointment the day before the appointment. The user can reschedule the appointment from the questionnaire screen. The questionnaire also asks whether the user went to the appointment on the day after.Adherence by participant to each of his or her own stated goals on that day.Using items from a drug use self-monitoring log developed by Sobell and Sobell [16], participants will be asked to report details of their drug and alcohol use within the last 24 hours, including drugs used, drinks had, cravings or urges to use drugs or drink alcohol, situations related to drug use (eg, patient was alone, in a social situation), and thoughts or feelings experienced when using drugs or during urges.

In the event of strong craving or substance use, the user is instructed to access an EMA screen bookmarked on his or her phone. The event-based EMA measures craving and surroundings at the time of craving or substance use.

Adapted from the 3-item Opioid Craving Scale by McHugh et al [31], participants will be asked to rate on a scale from 1 to 10 how much they currently crave a drug, how strong their desire to use has been when something in the environment reminded them of the drug, and the likelihood that they would use the drug in a specific environment.EMA items on psychological mood are adapted from an EMA assessment conducted by Gwaltney et al [32] and are designed to assess the participant’s affect state associated with substance use. The items ask participants to rate to what extent they feel happy, stressed, relaxed, bored, irritable, energized, and sleepy.

A risk score will be computed for every intervention participant every day. The score depends on the participant’s questionnaire adherence, self reported goal adherence, and substance use. If a participant is at high risk, he or she may be offered the brief intervention video to watch again.

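### On the natural record-level reading, the exploratory mood comparison applies chi-square or t tests to repeated EMA records as if they were independent; the GLMM in the same section does not replace them and does not model craving as an outcome

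*Protocol article*

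**What the plan says.** The Exploratory Analysis section first fixes who supplies the data: "we will collect self-reported mood and substance use/craving data from all intervention arm participants". It then names the comparison: "We will group substance use/craving data into positive and negative mood categories and compare the differences using chi-square or *t* tests", with the choice between the two tests left to whichever is appropriate.

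Other sections show that each participant supplies many records:

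- The introduction's section on EMA: "In EMA, subjects complete multiple assessments over time".
- Follow-Up, daily log: "The intervention arm participants will receive a once-per-day reminder to answer daily follow-up questions".
- Follow-Up, event reports: "In the event of strong craving or substance use, the user is instructed to access an EMA screen bookmarked on his or her phone".
- Timing and Flow: "The RCT tracks participants for 30 days after the primary care encounter".

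Table 1 schedules psychological mood and the craving scale under EMA, and substance use daily.

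After the simple tests, the Exploratory Analysis section continues: "Furthermore, we can apply multilevel (also called mixed effect) regression models to EMA data". It then describes one specific model, a generalized linear mixed model (GLMM) with binary substance use as the outcome and craving and mood states as fixed effects.

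**The concern.** Mood is a property of a record, so one participant can contribute records to both mood categories. What the text groups is data, not participants. Pearson's chi-square and the two-sample t test take their null distribution from independent observations. If some people are persistently in lower mood, and some people persistently crave or use more, the two categories contain different mixes of people. The categories can then differ by more than the test allows for, even when mood and outcome are unrelated. Participants who report more events also carry more weight.

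The article motivates this analysis by saying that existing evidence on mood and use or craving does not settle the question. A test that rejects above its nominal level does not help settle it. It may also disagree with the mixed model on the same records, and the text does not say that the model supersedes the simple tests.

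**Working it through.** The article gives no figure for the mood comparison, so there is none to reproduce. The check asks how often the named tests reject at two-sided 5% when there is no mood association.

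**Inputs from the article.** Power Calculation assumes equal arms, so 500 / 2 = 250 intervention participants, or 250 × 0.8 = 200 after the 20% attrition allowed for. Follow-up is 30 days. The 5% level is stated there for the primary hypotheses and is assumed here.

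**Inputs assumed.** The article gives neither the records per person (5, 10 and 30 tried, equal across people) nor the intraclass correlations (ICC) of mood and outcome on a latent scale (0.2/0.2, 0.3/0.4 and 0.5/0.5 tried, plus 0/0.4 with no clustering of mood).

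**Simulation.** Mood and outcome were generated independently of each other, each with a person effect. Mood was split at its median. The outcome was kept continuous for the t test and cut at its 70th percentile for the chi-square test. There were 1,000 runs per setting, so the Monte Carlo standard error is at most about 1.6 percentage points (√(0.5 × 0.5 / 1000)). Rejection rates with 250 participants, t test / chi-square:

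| ICC mood / outcome | 5 records | 10 records | 30 records |
|---|---|---|---|
| 0.2 / 0.2 | 6.0% / 5.7% | 8.6% / 7.6% | 12.6% / 11.2% |
| 0.3 / 0.4 | 7.5% / 6.6% | 12.0% / 9.6% | 24.5% / 18.3% |
| 0.5 / 0.5 | 13.5% / 10.5% | 21.3% / 16.0% | 42.4% / 33.0% |
| 0 / 0.4 | 4.3% / 5.6% | 6.2% / 5.0% | 6.0% / 5.6% |

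With 200 participants, 30 records and ICCs of 0.3/0.4, the rates were 29.3% / 20.9%.

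**Check by formula (t test).** With m records per person, the variance of the difference is inflated by about V = 1 + (m − 1) × ρx × ρy. Here ρy is the outcome ICC and ρx the ICC of the two-category mood variable, (2/π) × arcsin(latent ICC) for a median split. The rejection rate is 2 × Φ(−1.96 / √V).

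- ICCs 0.5/0.5: ρx = 0.333. With m = 10, V = 1 + 9 × 0.333 × 0.5 = 2.50, 1.96 / 1.581 = 1.240, rate 21.5% (simulated 21.3%). With m = 30, V = 1 + 29 × 0.333 × 0.5 = 5.83, 1.96 / 2.415 = 0.812, rate 41.7% (simulated 42.4%).
- ICCs 0.3/0.4: ρx = 0.194. With m = 30, V = 1 + 29 × 0.194 × 0.4 = 3.25, 1.96 / 1.803 = 1.087, rate 27.7%. This lies between the simulated 24.5% and 29.3%; the formula does not depend on the number of participants.
- No clustering of mood: ρx = 0, V = 1, rate 5%.

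**Unequal counts.** Event-triggered reports will not be equal in number. In a separate simulation with counts varying around a mean of 10, 200 participants and ICCs of 0.4/0.4, the rates were 16% (chi-square) and 23% (t test). The equal-count formula gives 16.0% for the t test at those ICCs (V = 1 + 9 × 0.262 × 0.4 = 1.94), so unequal counts raise the rate.

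**After correction.** On the data of the main simulation, a one-sample t test on each person's difference between mood categories rejected 3.3% to 6.1% of the time across all settings. In the unequal-count simulation, participant-clustered standard errors gave 4% to 7%.

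**The case against.** The strongest reply is that the section already contains a suitable model. A reader might infer from "Furthermore, we can apply multilevel (also called mixed effect) regression models to EMA data" that mixed models are only an option. That is not supported: the text goes on to specify a GLMM for use, and it gives reasons for mixed models, namely the range of outcome types, tolerance of missing data and unequal numbers of assessments. The simple tests could then be read as a descriptive first look. This stands in part and lowers the severity. But the simple tests are stated as a commitment, the mixed models are added without withdrawing them, and the specified model has use as its outcome and craving as a predictor. For craving as the outcome, only the general mention of mixed models remains.

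Second, the unit of analysis is not stated, and a condensed article may leave it to a fuller document. Pooling of records is therefore an inference. It is the natural one, because data are grouped by an attribute recorded at each event, but it should not be presented as the plan's own words.

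Third, a reader might infer 30 mood records per person from the daily log. The documents do not support that. Table 1 places mood and the craving scale under event-triggered EMA; the daily log touches on mood only through its item on thoughts or feelings when using or during urges. The 30-record column is best read as an upper case.

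**Conclusion.** The point holds in conditional form. On the record-level reading, the named tests ignore within-person correlation. They over-reject if mood and outcome both cluster by person: about 6% to 21% with 5 to 10 records each and about 11% to 42% with 30, for assumed ICCs of 0.2 to 0.5 and equal record counts. With few records and weak clustering the excess is small, and without clustering of mood there is essentially none (4.3% to 6.2%). A flat statement that the false-positive rate is several times nominal would go too far, because the article gives neither the ICCs nor the record counts.

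Nor does the point threaten the trial's main conclusions. The analysis is exploratory, uses the intervention arm only, and bears on neither primary hypothesis and none of the seven secondary hypotheses. Severity is minor. Correction is still worthwhile because the plan already names the method that is needed.

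**What to change.** - State the unit of analysis for the mood comparison.
- Drop the record-level chi-square and t tests as inference; keep the two-category figures as descriptive summaries at most.
- Make mixed models with a participant random intercept the analysis of the mood association: the logistic GLMM already described for substance use, and an added linear mixed model for the craving score.
- If a simple two-category comparison is still wanted, use participant-clustered standard errors. A paired test on each participant's mean outcome in the two mood categories is a weaker option: it drops participants who report only one category and targets a within-person effect.

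The cost is a sentence or two in the plan, slightly more analysis work and wider confidence intervals. No new data are needed, and the change can be made at any time before the analysis.
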